# Effect of Regular Consumption of a Miraculin-Based Food Supplement on Taste Perception and Nutritional Status in Malnourished Cancer Patients: A Triple-Blind, Randomized, Placebo-Controlled Clinical Trial-CLINMIR Pilot Protocol

**DOI:** 10.3390/nu15214639

**Published:** 2023-11-01

**Keywords:** taste disorders, dysgeusia, neoplasm, chemotherapy, *Synsepalum ducificum*, miracle fruit, malnutrition

## Abstract

Taste disorders are common among cancer patients undergoing chemotherapy, with a prevalence ranging from 20% to 86%, persisting throughout treatment. This condition leads to reduced food consumption, increasing the risk of malnutrition. Malnutrition is associated not only with worse treatment efficacy and poor disease prognosis but also with reduced functional status and quality of life. The fruit of *Synsepalum dulcificum* (Daniell), commonly known as miracle berry or miracle fruit, contains miraculin, a taste-modifying protein with profound effects on taste perception. The CLINMIR Protocol is a triple-blind, randomized, placebo-controlled clinical trial designed to evaluate the regular consumption of a food supplement containing a miraculin-based novel food, dried miracle berry (DMB), on the taste perception (measured through electrogustometry) and nutritional status (evaluated through the GLIM Criteria) of malnourished cancer patients under active antineoplastic treatment. To this end, a pilot study was designed with 30 randomized patients divided into three study arms (150 mg DMB + 150 mg freeze-dried strawberries, 300 mg DMB, or placebo) for three months. Throughout the five main visits, an exhaustive assessment of different parameters susceptible to improvement through regular consumption of the miraculin-based food supplement will be conducted, including electrical and chemical taste perception, smell perception, nutritional and morphofunctional assessment, diet, quality of life, the fatty acid profile of erythrocytes, levels of inflammatory and cancer-associated cytokines, oxidative stress, antioxidant defense system, plasma metabolomics, and saliva and stool microbiota. The primary anticipated result is that malnourished cancer patients with taste distortion who consume the miraculin-based food supplement will report an improvement in food taste perception. This improvement translates into increased food intake, thereby ameliorating their nutritional status and mitigating associated risks. Additionally, the study aims to pinpoint the optimal dosage that provides maximal benefits. The protocol adheres to the SPIRIT 2013 Statement, which provides evidence-based recommendations and is widely endorsed as an international standard for trial protocols. The clinical trial protocol has been registered at the platform for Clinical Trials (NCT05486260).

## 1. Introduction

Dysgeusia, a taste disorder typically characterized by an unpleasant and persistent taste, is often described as metallic, and other taste disorders are common among cancer patients [1]. While dysgeusia can have multiple origins, it is a common side effect for cancer patients who undergo chemotherapy and/or radiotherapy. The recovery from this disorder is a slow and gradual process and can take up to a year after treatment [2]. The incidence of dysgeusia depends on the type of treatment [3], with 45–84% of cancer patients receiving treatment experiencing this side effect [4]. Unpleasant flavors during meals can lead to changes in eating habits, poor nutrition, weight loss, and, ultimately, a decrease in morale, affecting the quality of life [5,6].

To date, the pharmaceutical and supplement industry has been unable to provide effective treatment or strategy for patients suffering from dysgeusia. Zinc supplementation [7,8,9], amifostine [10,11,12], selenium, lactoferrin, and cannabinoids are among the treatments used today, with limited clinically beneficial effects on taste disorders [13,14]. This scenario necessitates new clinical trials to identify effective strategies for controlling dysgeusia and improving the health and quality of life of patients [13,15].

*Synsepalum dulcificum* (Daniell), commonly known as “miracle fruit”, is a plant native to West Africa that contains miraculin, a glycoprotein that can transform sour flavors into sweet ones, making meals more palatable [16,17]. Thereby, miraculin acts as a selective agonist, at an acidic pH, or antagonist, at a neutral pH, of sweet taste receptors, depending on the food pH consumed [18]. Miraculin provides a high sweetness intensity; thus, its consumption could improve the perception of undesirable sour tastes in cancer patients with dysgeusia [19], improving food intake and, consequently, their nutritional status. In December 2021, the European Commission authorized dried miracle berries (DMB) as a novel food in the European Union [20]. DMB, officially cataloged as “dried fruits of *Synsepalum dulcificum*” in the EU, is the freeze-dried extract of the miracle berry’s pulp juice, which is rich in miraculin.

Previous studies have shown the potential of miracle fruit for treating taste disorders. A pilot clinical trial involving 23 patients with dysgeusia derived from chemotherapy treatment demonstrated that the consumption of this berry was safe, and 30% of patients showed an improvement in taste after two weeks of treatment [21]. Another pilot trial conducted two years later on eight patients who experienced taste disturbances after chemotherapy treatment showed that all patients demonstrated improvements in taste, with five patients reporting the disappearance of the metallic taste after supplementation with the fruit [22].

Despite the absence of substantial clinical evidence, prior uncontrolled pilot studies have hinted at the potential of using miracle fruit as a natural dietary supplement, presenting a promising nutritional strategy for managing dysgeusia. The current pilot study aimed to generate clinical evidence on the beneficial effect of the miraculin-based food supplement, containing the miracle fruit extract DMB, on taste disorders. Furthermore, the study sought to explore the interplay between this impact and the enhancement of patients’ nutritional status, employing a rigorous design and methodology. A comprehensive outline of the study’s protocol is provided in this article, adhering to the SPIRIT 2013 Statement (Supplementary Material File S1). This statement, recognized as an international standard for trial protocols (https://www.spirit-statement.org/spirit-statement/, accessed on 20 October 2023), offers evidence-based recommendations for the structure of clinical trial protocols.

## 2. Experimental Design

The CLINMIR study is a pilot randomized, parallel, triple-blind, and placebo-controlled clinical trial. The present protocol clinical trial was registered at http://clinicaltrials.gov, accessed on 20 October 2023, with the number NCT05486260.

### 2.1. Participants and Selection Criteria

A total of thirty malnourished cancer patients and taste disorders will be recruited by the Clinical and Dietary Nutrition Unit and Oncology Service of the Hospital University La Paz (HULP), Madrid (Spain).

The inclusion criteria include patients over 18 years of age with cancer and antineoplastic treatment (chemotherapy and any other treatment such as radiotherapy, immunotherapy, etc., for at least three months) who have a weight loss ≥ 5%, malnutrition assessed by the GLIM criteria [23], and taste disturbances measured by electrogustometry. Additionally, these patients must be starting or be in the first three months of antineoplastic treatment, have a life expectancy greater than 3 months, and be capable of oral intake of food and drinks. Patients also must be be at an appropriate cultural level and understand the clinical study, voluntary participation, and sign the informed consent form.

The exclusion criteria include patients participating in another clinical trial, with enteral or parenteral nutrition, poorly controlled diabetes mellitus (HbA1c > 8%), uncontrolled hypertension or hyper/hypothyroidism, severe digestive toxicity due to treatment with chemo-radiotherapy, severe kidney or liver disease (chronic renal failure, nephrotic syndrome, cirrhosis, etc.), severe dementia, brain metastases, eating disorders, a history of severe neurological or psychiatric pathology that may interfere with treatment, alcoholism or substance abuse, severe gastrointestinal diseases, and an unwillingness to consume the miraculin-based food supplement.

The withdrawal criteria include an inability to tolerate the ingestion of the miraculin-based tablets at any dosage or placebo.

### 2.2. Ethics and Dissemination

The final protocol was approved by the Scientific Research and Ethics Committee of the University Hospital La Paz. The research protocol in version 1 was approved in June 2022 (HULP Code 6164) in compliance with The Ethical Standards of the Declaration of Helsinki about the recommendations guiding physicians in biomedical research involving human subjects. All researchers are to know and follow the ICH Harmonized Tripartite Guidelines for Good Clinical Practice.

Before signing the informed consent form, all subjects will be informed by a study researcher about the study characteristics (verbally and in writing) and what their inclusion in the clinical trial means (File S2). Patients will be informed that they can decide at any time to abandon their participation in the study, notifying their doctor without having to give any reason and without detriment to their usual medical treatment. In this case, they will be asked if their decision is related to any adverse event due to the consumption of the miraculin-based tablets.

All study data will be processed by members of the research team in a database specifically created for this study and dissociated from any data that could identify the patient. The processing of personal data will follow the Spanish Organic Law (Ley Orgánica) 3/2018, of 5 December, and the General Data Protection Regulation of the European Union (EU) 2016/679 of 27 April 2016.

Only the study investigators will have access to the patient’s data with prior authorization from the principal investigator. Once the study is completed, all the data collected in paper format will be archived in the external archive store of HULP and will be kept for the period established by local legislation.

Once the clinical trial has finished, following the provisions of the Spanish Legislation (Real Decreto 1090/2015), the researchers and the promoter will publish the obtained results (positives or negatives). Publication will take place in a publicly accessible scientific journal.

### 2.3. Ancillary and Post-Trial Care

The patients will follow the usual intrahospital clinical practice once the study is completed. The patients will continue to be under the care of their treating physician at the La Paz University Hospital. The present clinical trial is a low-intervention study and no harm from trial participation is expected. 

### 2.4. Dissemination Policy

Trial results will be communicated via publication, reporting in results databases and other data-sharing arrangements. There will not be any publication restrictions. 

### 2.5. Interventions

Malnourished cancer patients in active treatment and with taste disorders will be randomized to one of three arms of the clinical trial. Over 3 months, each patient will dissolve a tablet of the miraculin-based food supplement five minutes before each main meal (breakfast, lunch, and dinner). Each tablet will contain DMB in one of its two doses or a placebo (Figure 1).

Alongside the standard dietary guidelines for cancer patients, participants will be motivated to incorporate acidic foods such as yogurt, vinegar, and lemon drops into their main meals. This approach aims to enhance compliance with the intervention. Each subject will be provided with the precise quantity of the miraculin-based food supplement bottles containing orally dissolving tablets with DMB or placebo necessary until their subsequent visit. Participants will be requested to return all packaging, whether empty or partially used, enabling compliance assessment through a comparison of provided and returned tablet quantities. Compliance will be established if a subject ingests ≥ 90% of the tablets supplied. In instances where the prescribed dose is not adhered to, the principal investigator will terminate the patient’s involvement in the study. Additionally, a dual product consumption monitoring mechanism is incorporated, involving a daily record where patients document the quantity and count of tablets consumed each day throughout the study.

Any pharmacological treatment undertaken during the follow-up period will be registered in an electronic Clinical Research Data Capture (eCRD) platform. Patients will maintain their regular treatment regimen. The use of any medication that does not interfere with the study formulation will be allowed. However, if there is any extraordinary medication, the principal investigator of the study will judge the suitability of the participant’s continued involvement.

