### 2.6. Treatments

Each intervention group will be integrated by 10 randomly assigned patients to one of two DMB dosages or placebo. The first arm will have 150 mg of DMB equivalent to 2.8 mg of miraculin + 150 mg of freeze-dried strawberries per orodispersible tablet; the second arm will have 300 mg of DMB equivalent to 5.5 mg of miraculin; and the third arm will contain 300 mg of freeze-dried strawberries per orodispersible tablet as placebo. The three treatments are isocaloric (Table 1). The subjects will be provided with as many tablets as necessary to complete the 3-month intervention period during recurring scheduled visits to the HULP.

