### 2.12. Data Collection and Management

The study data will be treated following the referenced confidentiality standards and the quality criteria described above. A specific database will be created in Microsoft Office Standard Excel 2013 (Microsoft® Company) using a standardized database creation process. All data collected in the research data collection will be entered by a member of the research team into the original database. This database will be designed with a double-entry system and filters to prevent and detect any type of inconsistency or error. Data will be incorporated based on the ID patient and visit where the results will be collected (vS, v1, v2, v3, v4, v5). The clinical trial Principal Investigator oversaw supervising the database construction. Databases will be stored in the HULP repository within the closed circuit, and RDC will be stored in the nutritionist’s office in a locked filing cabinet.

During the database creation process, a member of the research team will be in charge of notifying the principal investigator of the presence of missing values. These values will be those that for any reason have not been reflected in the RCD by the patient. The member of the research team indicated the affected cells in the database by coloring them yellow with the word “missing”. Once indicated, the sample size of the affected variable will be adjusted for subsequent statistical analysis. In no case will the patient record be deleted, only the missing value that affects the variable.

After incorporating all the data into the database, they will be duly cleaned, avoiding the appearance of symbols (<, >, etc.) that could interfere with the subsequent statistical analysis. The same member of the research team in charge of creating the original database will be in charge of creating a second database in which alphanumeric coding will be given to each variable to guarantee masking during data analysis. If so needed, new variables such as groupings or sums will be created to facilitate comparison between protocol main visits. When the database is finished, the Principal Investigator will oversee sending the Excel file to the Department of Biochemistry and Molecular Biology II (University of Granada) for analysis.

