## 5. General Characteristics of the Population

This section presents very preliminary results of the clinical trial. For the present study a total of 62 patients were evaluated for eligibility. Of them, 31 met the selection criteria and were randomized into three intervention groups (Figure 5). During follow-up, there were 10 dropouts, mainly due to the consumption of the supplement distorted the taste of some non-sweet acidic foods (n = 6) and because of the prescription added difficulty to their, already complex, antineoplastic treatment (n = 2). A final sample of 21 patients completed the clinical trial.

The sample was made up of 61.9% women and 38.1% men with a mean age of 59.8 ± 11.65 years old, all of them undergoing active treatment with chemotherapy and taste alteration measured by electrogustometry (Table 3). The average body mass index was 22.37 ± 3.67 kg/m^2^, classifying the patients as normal weight. However, the weight lost in the last 3 months was −7.60 ± 5.76%, with no significant differences between treatment groups. 

The most prevalent type of cancer was colorectal cancer (28.6%) followed by breast, lung, pancreas and liver cancers, each with 9.5%. Fasting glycemic control (105 ± 19 mg/dL) was within the normal reference parameters (74–106 mg/dL). The insulin concentration (12 ± 10 µU/mL) was normal in the entire population (3–25 µU/mL) as well as the lipid profile. All patients had systemic inflammation (CRP > 5 mg/dL). Both vitamins and minerals were found within the reference values except for vitamin D, which means blood concentration (21.25 ± 13.86 ng/mL) was insufficient (range 15–30 ng/mL).

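### Patients who miss the tablet-adherence requirement are taken out of the whole study, so follow-up depends on post-randomisation behaviour that the product itself can influence

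*Protocol article*

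**What the plan says.** Section 2.5 (Interventions) defines adherence by tablet count from returned packaging: "Compliance will be established if a subject ingests ≥ 90% of the tablets supplied". The consequence of falling short follows: "In instances where the prescribed dose is not adhered to, the principal investigator will terminate" the patient's involvement in the study. The object of the sentence is study involvement, not the tablets, and the article describes no further assessment of such patients.

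Section 2.1 gives a different ground for leaving: "The withdrawal criteria include an inability to tolerate the ingestion of the miraculin-based tablets at any dosage or placebo". The adherence threshold is not mentioned there.

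Section 2.12 deals with missing values: "Once indicated, the sample size of the affected variable will be adjusted for subsequent statistical analysis". It adds that the patient's record is kept and only the missing value drops out, which is available-case handling per variable.

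Section 2.7 sets the primary outcome as the change in electrogustometric threshold from v0 to v3, about one month into a three-month intervention. Section 2.8 runs the secondary outcomes to v5.

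Section 5 reports that "31 met the selection criteria and were randomized into three intervention groups" and that "there were 10 dropouts, mainly due to the consumption of the supplement distorted the taste of some non-sweet acidic foods (n = 6"), with 2 more leaving because of the added burden on their cancer treatment. It gives 21 completers. The characteristics in the text and in Table 3 are those of the 21.

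**The concern.** In a randomised comparison, patients should not stop being measured because of how they took or reacted to the product. Adherence is observed after allocation, and here the product can plausibly change it: it acts by altering taste, and some patients disliked that. Removing non-adherent patients from follow-up therefore lets the treatment influence who is measured, and randomisation no longer protects the comparison among those left.

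This is a rule fixed in the protocol, not a detail left for later. An analysis plan can define an all-randomised population, but it cannot recover v3, v4 or v5 assessments that were never made. Section 2.10 uses this pilot to size later efficacy trials, so a distorted effect or an unrepresentative variance would carry forward.

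**Working it through.** **1. The article's own counts.** Section 5 gives 31 randomised and 10 dropouts: 31 − 10 = 21, as stated. Table 3 shows 62.5%, 33.3% and 85.7% women. With a total of 21, the percentages in that table fit group sizes 8, 6 and 7, that is 5/8, 2/6 and 6/7. Together these give 13/21 = 61.9%, the figure in the text. Table 3 is therefore a completer table, although the planned allocation was: "Each intervention group will be integrated by 10 randomly assigned patients".

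**2. Dropout by stated reason** (denominator 31, Wilson 95% intervals).

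| Group | Share | 95% interval |
|---|---|---|
| All dropouts | 10/31 = 32.3% | 18.6 to 49.9 |
| Taste distortion | 6/31 = 19.4% | 9.2 to 36.3 |
| Taste distortion or regimen burden | 8/31 = 25.8% | 13.7 to 43.2 |
| No reason given | 2/31 = 6.5% | 1.8 to 20.7 |
| Attributed to the adherence rule | none stated | – |

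**3. Illustration of possible bias in the primary outcome.** The documents give no SD of change, so one is assumed.

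- Pooled baseline SD from Table 3: √[(7 × 12.46² + 5 × 15.88² + 6 × 15.71²)/18] = 14.58 dB. The SD of change equals this if the correlation between v0 and v3 is 0.5 (assumption), because SD × √[2(1 − 0.5)] = SD.
- Mean baseline threshold: (8 × 17.16 + 6 × 20.50 + 7 × 19.29)/21 = 18.8 dB.
- Further assumptions: no true effect, 20 patients on the two active arms, 6 of them lost before v3, none lost on placebo.
- If the 6 with the highest values of a normally distributed tendency to leave are lost from 20, the mean of that tendency among the remaining 14 falls by 0.476 SD (expected normal order statistics: the top six sum to 6.66, and 6.66/14 = 0.476).
- Bias = r × 0.476 × SD, where r is the correlation between that tendency and a worse threshold change.

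| r | Bias with SD 14.58 dB |
|---|---|
| 0 | 0 |
| 0.5 | 0.5 × 0.476 × 14.58 = 3.5 dB in favour of the product |
| 1 (the six worst responders leave) | 0.476 × 14.58 = 6.9 dB in favour of the product |
| −0.5 | 3.5 dB against the product |

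Over the range of group SDs in Table 3 (12.46 to 15.88 dB), r = 0.5 gives 3.0 to 3.8 dB. Against a mean baseline of 18.8 dB, the middle case is not negligible, but each row rests on inputs that the article does not supply.

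**The case against.** A reader might infer that the adherence rule caused the loss of a third of the sample for product-related reasons, and that the trial has become a comparison of completers. The documents do not support this.

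- **Cause.** Section 5 attributes no dropout to the 90% threshold. The stated reasons fit voluntary withdrawal (Section 2.2) or the intolerance criterion (Section 2.1) equally well, and rewording Section 2.5 might have kept none of the ten.
- **Fraction.** A third is right only for all dropouts. Product- or regimen-related reasons cover 6 to 8 of 31. Reaching 10 requires assuming that both unexplained dropouts were product-related.
- **Completers.** Section 2.12 keeps records and drops only missing values, so anyone who left after v3 still contributes to the v0 to v3 outcome. Adherence is counted from packaging returned at visits, so a patient found below 90% at v3 may already have attended v3. Neither the timing of dropout nor its split by arm is in the text; Figure 5 is not shown.
- **Direction.** Turning sour to sweet is the product's intended action. Nothing shows that disliking this goes with a worse electrical threshold, so the bias could be nil or reversed.
- **Status.** This is an exploratory pilot, Section 5 calls its results very preliminary, and the analysis population may be set in a plan not shown.

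All of this limits what can be claimed about the losses so far. It does not answer the point about the rule. Section 2.5 still makes follow-up conditional on adherence, and no later analysis plan can replace data that were not collected. The secondary outcomes, which run to v5, lose every patient terminated before then.

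**Conclusion.** The point holds in a limited form. Section 2.5 ends outcome follow-up for patients who do not adhere, and with available-case handling this pushes the comparison towards compliant patients. That follows from the text alone.

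The reported losses are a separate fact: 10/31 (32.3%) dropped out, 6/31 (19.4%) for taste distortion and 8/31 (25.8%) once regimen burden is added. They show that the product's effects drive leaving, not that the rule produced the losses. Even baseline characteristics are given only for the 21 completers.

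Size and direction of bias in the primary outcome are unknown. The values of 0, 3.5 and about 7 dB, with reversal if the correlation is opposite, depend on assumed arm, timing, SD of change and correlation, and serve only as illustration.

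**What to change.** - In Section 2.5, replace the end of study involvement with recording the patient as non-adherent and keeping the scheduled v3, v4 and v5 outcome assessments, unless the patient declines them. Whether tablets continue is a clinical decision and is not addressed here.
- Compare all randomised patients in their assigned arm, using every visit collected, including any from the 10 who dropped out. Keep the set with at least 90% adherence as a sensitivity analysis.
- Give baseline characteristics for all 31, and report dropout by arm, visit and reason.
- Reconcile the differing withdrawal rules in Sections 2.1 and 2.5.

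Cost: protocol wording and the remaining scheduled visits for a few patients, with no new procedures. The effect estimate will be somewhat diluted by non-adherent patients. For the ten who have already left, missed visits may not be recoverable, but using their collected data and rebuilding Table 3 remain possible.
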